##### Primary Outcome

The change in mean depressive symptoms will be assessed by a planned comparison of the difference between groups in the change of PHQ-9 scores from baseline to postintervention using a linear mixed model for repeated measures. This test will be undertaken with an α of .05. Models will include factors of intervention arm (intervention or control group), occasion of measurement (time points 1, 2, and 3), and their interaction. An unstructured residual variance-covariance matrix will accommodate within-participant dependency. Tests of significance will use the Kenward-Roger method of df adjustment based on the observed information matrix. Where necessary, transformation of the outcome variable will be undertaken to ensure the distributional assumptions of the model are met.

Depression caseness will be estimated using the established threshold for moderate depressive symptoms using the PHQ-9 total score (a score of 10 or greater). Odds ratios and predicted probabilities will be obtained from a generalized logistic mixed model, which will include random participant intercepts and the factors used in linear models. This will allow us to determine the app’s effectiveness in reducing symptomatic status in participants who are likely to have depression, as well as investigate whether the participants who are mentally healthy were able to stay well after the app use.

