## Methods

### Study Design

The study is a 2-arm parallel RCT. Randomization is not stratified and will automatically occur when a participant completes the baseline questionnaire. The study will be carried out entirely on the internet and will not be blinded due to the nature of the intervention.

Junior physicians will be randomly allocated to one of two groups, namely, (1) the intervention group or (2) the control group. The intervention group will be provided with a link to download the Shift mHealth app; the participants in this group will be asked to use the app for a period of 30 days. The control group will be placed on a waitlist and will be asked to use the app after 3 months. Participants allocated to the control group are provided with a factsheet that lists several mental health support services, which they are encouraged to contact for further support. These participants will gain access to Shift after 3 months and will be asked to use the app for 30 days.

Primary and secondary outcomes will be measured through self-assessment using questionnaires at 3 time points: the first distributed as part of the baseline assessment, the second distributed 30 days after the baseline assessment, and the third distributed 3 months after the baseline assessment. Waitlist control participants will be further asked to respond to a questionnaire measuring primary and secondary outcomes after 4 months following the baseline assessment or 1 month after they gain access to the app. This will enable us to compare the 30-day app use patterns of the control group with those of the intervention group who used the app in the first month of the trial.

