##### Sample Size

We determined a total sample size of 778 research participants. Power calculations were based on a recent systematic review and meta-analysis quantifying the efficacy of digital prevention interventions for depression [29]. Hence, an estimated Cohen *d* effect size of 0.25, an α value of .05, a power of 0.8, and a correlation coefficient of 0.6 yielded the required sample size of 404, without any participant dropouts.

A systematic review and meta-analysis examining dropout rates during clinical trials of smartphone apps for depressive symptoms found a pooled dropout rate of 48% [30]. Therefore, we expect to randomize a total of 777 participants (N=404+373) to the 2 trial conditions to conduct a sufficiently powered analysis. To allow for evenly sized groups, this number was rounded off to 778 participants.

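### The primary model is valid but estimates a baseline arm difference that randomisation makes pure chance, giving up about 11.5% of variance on the plan's own inputs

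*Protocol article*

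**What the plan says.** The Primary Outcome section of the protocol article sets the primary test as follows: "planned comparison of the difference between groups in the change of PHQ-9 scores from baseline to postintervention using a linear mixed model for repeated measures". It gives the fixed effects: "Models will include factors of intervention arm (intervention or control group), occasion of measurement (time points 1, 2, and 3), and their interaction". It gives the covariance: "An unstructured residual variance-covariance matrix will accommodate within-participant dependency". It names Kenward-Roger degrees of freedom, and on the test level it says "This test will be undertaken with an α of .05". It mentions neither a baseline covariate nor a common baseline mean. The Secondary Outcomes section carries the same strategy over to GAD-7, the Work and Social Adjustment Scale (WSAS), the Linear Analog Scale Assessment (LASA) and the Oldenburg Burnout Inventory (OLBI), and also looks at change to time point 3.

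The Study Design section fixes the order of events: "Randomization is not stratified and will automatically occur when a participant completes the baseline questionnaire". The Sample Size section assumes "an estimated Cohen *d* effect size of 0.25" and then "a power of 0.8, and a correlation coefficient of 0.6 yielded the required sample size of 404, without any participant dropouts". It allows for 48% dropout and arrives at 777 randomised, rounded to 778.

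**The concern.** Baseline PHQ-9 is measured before allocation, so the true arm means at time point 1 are equal by design. The stated model does not use this fact. It has a free arm effect at time point 1, and its contrast removes the observed baseline difference from the post-intervention difference.

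With complete data that removal has weight 1, whereas the plan's own correlation implies an optimal weight of 0.6 (equal variances assumed at the two occasions). The excess weight adds noise and nothing else. At stake is the precision of the primary estimate and of every continuous secondary outcome analysed the same way, in a trial that expects to lose almost half of its follow-up data.

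**Working it through.** **Inputs.** Effect d = 0.25, correlation r = 0.6, power 0.8, α = .05 and 48% dropout come from Sample Size and Primary Outcome. The 778 randomised are taken as 389 per arm. Follow-up is 0.52 × 389 ≈ 202 per arm. Assumptions of this check: two-sided test (the article does not state the side), SD = 1 at each occasion, and dropout completely at random and equal in the two arms.

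**Step 1: reproduce the plan's figure.** With complete data, the variance per participant is:

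| Analysis | Variance | Total N (normal approximation) | Total N (noncentral t) |
|---|---|---|---|
| Post score only | 1 | 504 | 506 |
| Change score | 2(1 − 0.6) = 0.80 | 402 | 404 |
| Common baseline mean | 1 − 0.6² = 0.64 | 322 | 324 |

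The plan's 404 is exactly the change-score size, and 404/0.52 = 776.9, which rounds up to 777. The sample size and the planned test therefore agree with each other.

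**Step 2: the complete-data bound.** The variance ratio is 0.64/0.80 = 0.80, a 20% saving. At 404 complete participants, power would rise from 80% to 88%. This is not the expected situation, because it supposes no loss to follow-up.

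**Step 3: with the planned dropout.** Let n be baselines and m follow-ups per arm. The contrast variances are:

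- planned model: 2[(1 − r²)/m + (1 − r)²/n]
- common time point 1 mean: 2(1 − r²)/m

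With r = 0.6, n = 389, m = 202:

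- planned: 2[0.64/202 + 0.16/389] = 0.00716, SE 0.0846, power 84.0%
- constrained: 2 × 0.64/202 = 0.00634, SE 0.0796, power 88.1%
- variance ratio 0.885, a saving of 11.5%; 1/0.885 = 1.13, so it is worth about 13% more follow-ups.

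The saving is smaller than 20% because, with dropout, the planned likelihood model already adjusts the followed-up outcomes for baseline with weight r. Only the remaining 1 − r = 0.4 falls on the baseline difference among all randomised.

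A simulation of 20,000 trials gave empirical standard deviations of 0.0845 and 0.0798, and mean estimates of −0.2505 and −0.2504 against a true −0.25. Both estimators are unbiased.

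**Step 4: range over the correlation** (389 randomised and 202 followed up per arm):

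| r (assumed) | SE planned | SE constrained | Variance saving | Power planned | Power constrained |
|---|---|---|---|---|---|
| 0.4 | 0.1008 | 0.0912 | 18.2% | 69.8% | 78.3% |
| 0.5 | 0.0933 | 0.0862 | 14.8% | 76.4% | 82.7% |
| 0.6 | 0.0846 | 0.0796 | 11.5% | 84.0% | 88.1% |
| 0.7 | 0.0742 | 0.0711 | 8.4% | 92.0% | 94.0% |
| 0.8 | 0.0614 | 0.0597 | 5.5% | 98.3% | 98.7% |

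Steps 3 and 4 use time points 1 and 2 only. If dropout is monotone, time point 3 adds nothing to the time point 2 contrast. Other missingness patterns would move the figures slightly, and the article does not describe the pattern.

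**The case against.** The strongest reply is that nothing in the plan is wrong. Arm, occasion and their interaction with an unstructured covariance is a standard model. It is unbiased under randomisation, it controls type I error, and the trial was sized for exactly this test. On the stated inputs power is already about 84%, above the 80% target. All of that stands. It does not remove the gain: the constrained variance is smaller at every correlation below 1 and needs no further data.

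Four stronger readings are tempting, and the documents do not support them.

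- **That the trial is underpowered, or that power would rise from 80% to 88%.** The first contradicts Step 3. The second holds only with complete data, while the plan expects 48% dropout.
- **That regression to the mean after a chance imbalance is a further harm.** It is the same variance counted again. At r = 0.6 the typical shift is 0.4 × √(2/389) = 0.029 SD, which is already inside the SE of 0.0846.
- **That the planned model loses participants who have baseline data only.** Time point 1 is an outcome occasion in that model, so they are kept.
- **That the change costs nothing.** The Results section says data collection ran to August 2024 and analysis was underway in September 2024, and the trial is unblinded. Replacing a primary model at that stage has a prespecification cost. In addition, the Data Exclusion section removes participants who withdraw and refuse use of their data. If such removals differ by arm, equal baseline means are no longer assured in the analysed set.

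**Conclusion.** The point holds as one of lost efficiency, with no bias and no inflated error rate. The planned primary test is valid and consistent with its sample size, but it spends precision on a baseline difference known to be zero in expectation. On the plan's inputs the cost is 11.5% of variance and about four percentage points of power.

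The gain matters most if the true correlation falls below the planned 0.6, where the planned test would miss its 80% target: at 0.5 the common-mean model brings power back above 80%, and at 0.4 nearly so. At 0.8 the gain is negligible. These figures rest on a two-sided α of .05, equal variances at the two occasions, equal arms, and loss to follow-up unrelated to outcome or arm. The change is worth making, but the primary result would stand without it.

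**What to change.** Drop the arm effect at time point 1. Keep the occasion effects, the arm-by-occasion terms at time points 2 and 3, the unstructured covariance and Kenward-Roger. Take the arm term at time point 2 as the primary estimate. Use the same form for GAD-7, WSAS, LASA and OLBI.

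This costs one change to the model statement and no new data. Because analysis had begun, record and date the change before any comparison between arms is seen. If that is no longer possible, keep the planned model as primary and report the common-baseline model as a labelled sensitivity analysis. In either case, report by arm how many participants were removed under Data Exclusion, and check that these removals do not differ between arms before relying on the constraint.

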##### Secondary Outcomes

Group differences on secondary outcomes on the GAD-7, Work and Social Adjustment Scale, Linear Analog Scale Assessment, and Oldenburg Burnout Inventory scales will follow the same analysis strategy that is used for the primary outcome. For the categorical secondary outcome measure (modified General Help Seeking Questionnaire), analogous generalized mixed models will be used.

Secondary analyses will also include changes in the primary and other outcome variables from baseline (time point 1) to follow-up (time point 3) to establish retention of any benefit. The waitlist group will be provided with access to the intervention after follow-up at time point 3. Postintervention outcomes in the waitlist group (time point 4) will be compared with the intervention group’s postintervention (time point 2) scores to estimate changes after they have accessed the intervention. Subject to qualifications arising due to attrition and any natural drift with the passage of time, this analysis will stand as a quasi-replication of the primary outcome of the trial.

As participant sample size allows, a priori defined subgroup analyses (focusing on age, sex, specialty, training level, and location) will be conducted to explore how the primary and secondary outcomes are affected by app use, baseline symptoms patterns (severity of depression and anxiety symptoms), and related factors (eg, self-reported wellbeing status) across all examined time points to inspect group and subgroup trajectories.

Qualitative, open-ended feedback responses will be examined to aid subsequent app changes and future study design considerations. Individual data collected in the questionnaires will be assessed using a structured tabular thematic analysis approach for brief texts, as outlined in Robinson [28].

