### Procedure

The procedure for the Shift RCT is depicted in Figure 2. At the study sign-up, candidates will be invited to visit a study-specific website [24]. Through the website, they will be presented a brief overview of the study purpose and the full participant information statement and consent form. The candidates who are willing to participate will be able to self-screen for eligibility. All the eligible participants will then be presented with a registration page in which they will be asked to input their first name, email address, mobile number, and password.

Following registration, the participants will be asked to complete a survey assessing the primary outcome (depression) and secondary outcomes (anxiety, work and social functioning, quality of life, burnout, and help-seeking intentions and behaviors). After completing the baseline survey, the participants will be randomly assigned to (1) the intervention group (in which a link will be provided through which they can download and use the app, immediately after registration) or (2) the waitlist control group (the members of will be added to a waitlist to use the app). The participants in the waitlist control group are provided with a factsheet listing contact details for several mental health support services and are encouraged to reach out if they would like further support. After the 3-month study period, the participants in the control group will also gain access to the app and will be asked to use it for 30 days. After the participants are provided with a link to download the Shift app on their smartphone, they will be able to use the app free-of-cost.

The primary and secondary outcomes will be measured in both the control group and the intervention group at a number of time points: at baseline and registration (time point 1), 30 days after registration (time point 2), and 3 months after registration (time point 3). These outcomes will also be measured among participants in the control group after 4 months following registration (time point 4), that is, once the participant has had access to the app for 30 days. At each follow-up measurement time point, the participants will receive an initial email reminder to complete the study. This will be followed by an email, a text reminder after 2 days and a text reminder after 9 days.

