### Data Analysis

#### Estimands and Statistical Analysis

##### Estimands

The primary estimand [25] will reflect intention-to-treat principles and will be based on all participants in the group to which they were randomized regardless of actual receipt, uptake of the intervention, alternative support or interventions received, and withdrawal from the study. A mixed-model, repeated measures analysis will be used for the primary outcome and continuously scaled secondary outcome variables to estimate and compare the change in mean PHQ-9 score in each intervention arm from time point 1 to time points 2, 3, and 4 (if applicable). This form of analysis assumes that unobserved outcome data are missing at random.

As substantial attrition is expected given the distal, universal nature of the intervention, a sensitivity analysis of the primary outcome will be undertaken if the outcome of the intention-to-treat is statistically significant. The “jump-to-reference” approach will be used [26]. This approach assumes that the participants who withdraw or have no postbaseline data have the same trajectories as participants in the control condition. This will yield a robust, conservative lower bound estimate of the intention-to-treat effect in the presence of missing outcome data.

Secondary estimands will estimate the treatment effect in participants who have engaged with the Shift app to various extents. Given that app users are free to choose the modules they use and to access them as often as desired, the concept of full compliance is not applicable. One estimate will involve participants who complete the recommended 8 or more modules during the intervention. The second estimate will broaden engagement to participants who have completed at least 4 modules. This reflects the levels of engagement more commonly observed in the previous version of the app [14]. The complier average causal effect comparing *compliers* in the intervention group to *would-be compliers* in the control group will be estimated using latent variable methods [27]. A conventional per-protocol analysis, including only participants allocated to the intervention group who have downloaded the app, will also be conducted.

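### The waitlist T4 versus intervention T2 comparison sets app against app, so taken alone it cannot be a quasi-replication of the primary result

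*Protocol article*

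**What the plan says.** T1 to T4 stand for time points 1 to 4 (baseline, 30 days, 3 months, 4 months).

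- **The contrast.** Secondary Outcomes, under Data Analysis, says: "Postintervention outcomes in the waitlist group (time point 4) will be compared with the intervention group’s postintervention (time point 2) scores".
- **Its purpose.** The same sentence gives the aim as "to estimate changes after they have accessed the intervention".
- **Its status.** The next sentence gives its standing relative to the primary outcome: "Subject to qualifications arising due to attrition and any natural drift with the passage of time, this analysis will stand as a quasi-replication". The plan therefore names attrition and drift as limits itself.
- **Exposure at T4.** Secondary Outcomes says: "The waitlist group will be provided with access to the intervention after follow-up at time point 3". The Procedure section places T4 at the moment "once the participant has had access to the app for 30 days". So T3 is the waitlist group's last app-free measurement.
- **Exposure at T2.** Under Study Design and Procedure, the intervention group gets the app straight after baseline and is measured at 30 days.
- **What would be replicated.** The Primary Outcome section tests the between-arm difference in PHQ-9 change from baseline to postintervention, that is, app against no app. Its model uses "occasion of measurement (time points 1, 2, and 3").

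**The concern.** A replication of the primary result has to ask the same question again: do people with the app do better than they would without it? The stated comparison has no measurement without the app on either side. The waitlist group's T3 score, the natural reference for a change after access, does not enter it. The purpose (a change) and the contrast (one post-app score against another) do not match.

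At stake is how a null result is read. Similar scores at waitlist T4 and intervention T2 look like the same benefit reached twice, but an inert app would also be expected to give similar scores. The caveats do not cover this. They treat attrition and drift as disturbances around an informative contrast, whereas under an equal effect those disturbances, together with repeated-testing effects, are all that the contrast contains.

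**Working it through.** **Inputs from the Sample Size section.** Effect size d = 0.25, alpha .05, power 0.8, correlation 0.6, 404 participants before dropout, 48% dropout. Assumptions not in the article: two-sided test, SD 1, equal correlation of 0.6 between all occasions, no attrition beyond the 202 per arm analysed, and the drift values below.

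**The plan's own figure.** With a change-score variance factor of 2(1 − 0.6) = 0.8:

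n per arm = 2 × (1.96 + 0.84)² × 0.8 / 0.25² ≈ 201, or 402 in total, against 404 stated.

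Dropout: 404 / (1 − 0.48) = 776.9, so 777, as stated. The plan's numbers hold, and 404 / 2 = 202 per arm is used below.

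**Algebra.** Let μ be the common baseline mean, D the fall in score due to 30 days of app access, and drift(m) the change by month m without the app.

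- Waitlist at T4: μ + drift(4) − D
- Intervention at T2: μ + drift(1) − D
- Difference: drift(4) − drift(1)

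D cancels. On change from baseline, μ is subtracted from both lines and the difference is the same. If the effects differ (D_W in the waitlist group, D_I in the intervention group), the difference gains D_I − D_W, which says whether the effects differ and not whether either is above zero.

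**Simulation** (202 per arm, 4,000 runs, same D in both arms). Each cell gives the mean contrast in SD and the share significant.

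| Contrast | D = 0 | D = 0.25 | D = 0.5 |
|---|---|---|---|
| Planned, scores, no drift | 0.00, 4.8% | 0.00, 5.1% | 0.00, 5.0% |
| Planned, change from baseline, no drift | 0.00, 5.0% | 0.00, 4.4% | 0.00, 5.1% |
| Planned, scores, drift −0.03 SD per month | −0.09, 15.1% | −0.09, 14.4% | −0.09, 13.8% |
| Primary, T1 to T2, no drift | 0.00, 4.7% | −0.25, 80.3% | −0.50, 100% |
| Waitlist T3 to T4, no drift | 0.00, 5.2% | −0.25, 97.9% | −0.50, 100% |

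The planned contrast moves with drift (3 months × −0.03 = −0.09) and not with D. The waitlist group's own T3-to-T4 change does move with D, but it is uncontrolled: the same drift shifts it by −0.03.

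**Setting T3–T4 against T1–T2 in the same people.** Both intervals are about one month, so a linear drift cancels: (drift − D) − drift = −D. The price is precision. The variance is 4(1 − 0.6) = 1.6, the standard error is √(1.6/202) = 0.089, and at D = 0.25 z = 0.25/0.089 = 2.81. Power is Φ(2.81 − 1.96) ≈ 0.80, against 98% for the T3-to-T4 change alone.

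**The case against.** **The article hedges.** It says quasi-replication, not replication, and names attrition and drift in the same sentence. That stands, and it lowers the severity. It does not cover the cancellation of the app effect.

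**The analysis would be read beside the primary result, not alone.** This has some force. Given a significant primary result in favour of the app, and no drift, the change-from-baseline version averages about +0.16 SD with 38% significant if that result was a false positive (D = 0). It averages about +0.02 SD with 4% significant if D = 0.25. On raw scores, the form the article names, the separation is weak: about +0.05 against +0.01 SD. So the contrast is a poor check rather than an empty one when read in sequence. The point is limited to what it can show alone.

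**The aim of estimating changes implies a waitlist pre-post analysis, with details left to the analysis plan.** An unseen plan may say more. But the article names a specific contrast and gives it a specific status, and the two do not fit. This is not an omission.

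**Stronger readings that a reader might infer.**

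- That the Estimands section contradicts the primary model by listing change "from time point 1 to time points 2, 3, and 4 (if applicable"). It does not: T4 exists only for the control group, and the qualifier covers that.
- That the sponsor will declare replication from a null difference. No such decision rule is stated; the risk lies in the label.
- That the contrast gives the same answer in every circumstance. The cancellation holds in expectation and for equal effects only.

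**Conclusion.** The concern holds for this one secondary analysis. The comparison is app against app. With an equal 30-day effect in both arms its expected value does not depend on that effect, and about 5% of trials are significant without drift at 0, 0.25 or 0.5 SD alike. Taken alone, it cannot replicate the app-versus-no-app result.

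The cancellation rests on the equal effect, not on the simulation settings. The percentages also rest on 202 analysed per arm, the correlation of 0.6 at all occasions and, where used, an assumed drift. The article gives no drift figure and no expected number of T4 respondents, so the 14–15% under drift is an illustration.

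Severity is moderate. The primary test, its alpha and the sample size are untouched, and a reader should not infer that the trial's main conclusion is at risk.

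**What to change.** In Secondary Outcomes:

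1. Replace the contrast with the waitlist group's own change from T3 to T4, set against the same participants' untreated change in one mixed model. T1 to T2 is the natural reference because it also spans about one month; T2 to T3 would need scaling for its longer interval. Report the estimate beside the intervention arm's T1-to-T2 change.
2. Call it an uncontrolled pre-post supportive analysis and drop the quasi-replication label. Keep the attrition and drift caveats.
3. Keep T4 against T2, if wanted, only as a description of whether post-app scores are similar in the two groups.

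The Estimands section and the primary model need no change.

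Cost: no new data, one re-specified contrast and a weaker label. The analysis stays uncontrolled, and drift that is not linear (for example, early recovery after enrolment) would not cancel. Because analysis was under way in September 2024, the change has to be dated and disclosed in the results report as made after data collection.
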